## Abstract

**Background:**

In times of increasing mental health problems among young people, strengthening efforts to improve mental health through mental health promotion and prevention becomes increasingly important. Effective measures that support young people in coping with negative thoughts, feelings, and stress are essential, not just for the individual but also for society.

**Objective:**

The aim of this paper is to provide a description of a cluster randomized controlled trial that will be conducted to examine the effectiveness of Opp, a universal mental health–promoting mobile app for adolescents aged 13 to 19 years that provides information and exercises to better cope with stress, negative thoughts, and negative feelings. The protocol was developed in accordance with the SPIRIT checklist.

**Methods:**

An effectiveness study will be conducted with 3 measurement points: preintervention (T1), 2 weeks after the intervention (T2), and about 1 month after the intervention (T3). Adolescents will be recruited from middle and high schools in Norway and randomly assigned to the intervention or control groups. Randomization will be conducted on the school level. Opp can be downloaded from the Google Play or App Store but is password protected with a 4-digit code, which will be removed after study completion. Participants in the intervention group will receive a text message with the code to unlock the app. The participants in the intervention group can use Opp without limits on length or time of use. Objective data on how long or how often the participants use the app will not be collected. However, the second and third questionnaires for the intervention group contain app-specific questions on, for example, the use of the app.

**Results:**

Recruitment and data collection started in August and September 2022. So far, 381 adolescents have answered the first questionnaire. Data collection was expected to end in December 2022 but has had to be prolonged to approximately June 2023. The results of the study will be available in 2023 at the earliest.

**Conclusions:**

This project will contribute unique knowledge to the field, as there are few studies that have examined the effects of universal health-promoting mobile apps for adolescents. However, several limitations have to be taken into account when interpreting the results, such as randomization on the school level, the short time frame in which the study was conducted, and the lack of objective data to monitor the use of the app.

**Trial Registration:**

ClinicalTrials.gov NCT05211713; https://www.clinicaltrials.gov/ct2/show/NCT05211713

**International Registered Report Identifier (IRRID):**

PRR1-10.2196/42119

## Introduction

### Background

The World Health Organization defines mental health as a “state of well-being in which the individual realizes his or her own abilities, can cope with the normal stresses of life, can work productively and fruitfully, and is able to make a contribution to his or her community” [1]. Good mental health is essential to good health in general and is strongly related to quality of life and participation in school and leisure activities. A scoping review that underlined how difficult it is to define and operationalize good mental health identified 14 core domains of good mental health in young people, including attitudes toward mental disorders, self-perceptions, emotions, behaviors, self-management strategies, social skills, family and significant relationships, and quality of life [2]. The authors wrote that mental health promotion “leads to increasing well-being, competence and resilience and makes individuals improve their mental health and increase their control over it” [2]. Mental health promotion focuses on promoting the positive factors associated with mental health. On the individual level, these factors are, for example, coping with negative thoughts, negative feelings, and stress, as well as increasing resilience and self-esteem [3]. The World Health Organization defines health promotion as “the process of enabling people to increase control over, and to improve their health” [4].

It is widely acknowledged that public health work should focus on universal health-promoting and preventive measures rather than on the treatment of disorders [5,6]. Preventing mental disorders and promoting good mental health is more cost-effective for society and has greater benefits for public health [7]. Working preventively and promoting good mental health is particularly important for young people. On the one hand, adolescence is a vulnerable period in which young people transition from being children to being adults; many mental disorders develop during this period [8]. On the other hand, adolescence is a time when young people can learn and adopt healthy habits and choices from which they can benefit throughout their lives.

In order to reach adolescents, mental health–promoting interventions should be conducted where adolescents actually spend their time. This can, for example, be at schools, at places where adolescents carry out their leisure activities, or online. In Norway, most adolescents have their own smartphones, which they use daily and often for multiple hours [9]. This may open new opportunities to implement mental health–promoting interventions through mobile apps. Despite potential barriers, apps can reach a large proportion of adolescents. This is especially important in countries like Norway that are geographically large and where health services are not always easily accessible. Furthermore, apps are also cost-effective and might be appealing to adolescents, who have a relatively high threshold for seeking help face-to-face [10]. Adolescents prefer to be anonymous, and app-based interventions may therefore be important for promoting good mental health [11]. Also, adolescents often look for health-related information online [9]. However, the quality of the information they find can vary. It is therefore important to offer information that is both high quality and easily accessible to adolescents, especially when it comes to mental health.

Reviews from 2013 and 2014 [12,13] concluded that digital self-management resources were promising, but that there was a need for more research. A recently conducted meta-review that synthesized the results of 14 meta-analyses concluded, on the other hand, that mobile phone–based interventions already have potential for mental health promotion, especially when it comes to reducing psychological symptoms (ie, stress, anxiety, and depression) and increasing quality of life [14]. Although the effects of apps are generally of small magnitude, they could have an important societal impact if they were made available to large groups.

Kenny et al [15] conducted the first and, to the best of our knowledge, only cluster randomized controlled trial to examine the effectiveness of a mental health mobile app–based intervention in a general population of adolescents. They recruited 560 subjects aged 15 to 18 years from 10 schools that were randomly assigned to an intervention or control condition. Participants in the intervention group used the app for about 4 weeks. However, no significant differences in well-being, emotional distress, emotional self-awareness, or coping strategies were found.

One of the largest cluster randomized controlled trials of the effectiveness of universal school-based mindfulness training on mental health and well-being in early adolescence, the MYRIAD (My Resilience in Adolescence) project, found no evidence that it was more effective than the provision of usual social-emotional learning [16]. A meta-analysis of the effectiveness of relaxation techniques to reduce distress, anxiety, and depression in adolescents, on the other hand, had promising results with small to moderate effect sizes [17].

Identifying effective interventions for improving mental health among adolescents is necessary, and studies that have no or negative results also play an important role in determining what helps to improve mental health and what does not [18]. Or as Kuyken et al [16] conclude, “There is need to ask what works, for whom and how, as well as considering key contextual and implementation factors.”

### The Current Paper

The aim of the current paper is to describe a cluster randomized controlled trial that will be conducted to evaluate the effectiveness of Opp. Opp is a universal mental health–promoting mobile app for adolescents that provides information about mental health, feelings, and help seeking, as well as exercises and techniques to better cope with negative thoughts, negative feelings, and stress.

Opp is part of the research project UngRisk, which aims to develop and evaluate 2 mental health–promoting mobile apps that will be made available as free resources for easy access by young people. The other mobile app is called NettOpp and is aimed at young people aged 11 to 16 years who have experienced negative incidents online. A study similar to the one that is described here has already been conducted to examine NettOpp’s effectiveness [19]. Data analysis is in progress.

## Methods

### Eligibility Criteria and Setting of the Effectiveness Study

Both the adolescents and participating schools are convenience samples. Adolescents aged 13 to 19 years are eligible for participation in the study and will be recruited through middle and high schools in Norway.

### Inclusion and Exclusion Criteria

Adolescents aged 13 to 15 years need consent from their guardians, while adolescents that are 16 years or older can consent for themselves. Adolescents need a smartphone to use the app and need to be able to read Norwegian.

### Intervention

Opp is a universal mental health–promoting mobile app that is aimed at adolescents aged 13 to 19 years. The Norwegian word *opp* means “up” in English. In Norwegian, *opp* also evokes the word *opplysning*, which means “enlightenment” or “information”; *opp* also evokes the word “uplifting,” meaning to lift someone’s spirit.

The overall goals of Opp are to (1) increase well-being and mental health, (2) increase knowledge about mental health, (3) increase coping skills to deal with stress, (4) increase help-seeking behavior, (5) increase self-esteem, (6) increase sleep quality, and (7) reduce mental health problems.

To achieve these goals, Opp is theoretically divided into psychoeducational and resource modules (modules 1 and 2, respectively). Module 1 contains information about mental health (eg, “What is mental health?” “How are thoughts, feelings, and behavior connected?” “Why is good mental health important?” “How to get and maintain good mental health?” “What are mental health problems?” and “When should one seek help for their challenges?”), about feelings (eg, “What are feelings?” “Why are feelings important?” “Can you control your feelings?” and “What do you do when feelings take over?”), and about help seeking (eg, “When should you seek help?” “How to tell somebody about problems?” “What should happen when you have told somebody about your problems?” and “Here you can get help”).

Module 2 provides exercises and techniques on how to cope with difficult thoughts, feelings, and stress. For the latter, exercises include breathing and meditation exercises with animation and sound. Another exercise is inspired by cognitive behavioral therapy and aims at helping adolescents to recognize and challenge negative thoughts. Adolescents are guided through this exercise and can choose different statements (eg, “Nobody likes me”), how this thought makes them feel (eg, “sad”), and alternative thoughts (eg, “There are people who love and care about me”). In addition, there is an exercise in which the adolescents can choose different situations, choose what they might think and feel if they were in such situations, and choose how they would behave. This exercise also aims at raising awareness about the relationship between thoughts, feelings, and behavior. In addition, the app contains sleep hygiene advice, tips for maintaining good social relationships, and suggestions on how to increase self-esteem. The information is displayed through text, sound, and animation.

Opp can be downloaded from the Google Play and App Store, but the app is password protected. The password will be removed after study completion to make the app freely available to all users. Adolescents in the intervention group that have answered the first questionnaire can install Opp on their phone and will be provided with a 4-digit code via text message to unlock the app. It is up to the young people themselves to decide when they want to use the app and how much time they want to spend using it. It is not possible to monitor how much time the adolescents actually spend using Opp. However, there are app-specific questions in the second and third questionnaires, which the adolescents will be asked to fill in after approximately 2 and 4 weeks, respectively, that ask how often the adolescents have used the app. The participants are not provided with any training in using the app, but are instructed via text message on how to download the app. Also, the participants are given a phone number that they can call or send a text message to if they experience any problems with downloading or using the app.

### User Involvement

Users, that is, adolescents aged 13 to 19 years, were involved in the project from the development of the content of the intervention to its evaluation. Approximately 15 adolescents were involved in 2 workshops to provide input on the content, design, and name of the app. Two adolescents critically read through a manuscript that described the content of Opp and provided feedback on wording and terminology. There was also an extended reference group consisting of teachers, school-health nurses, nurses from a health care center for adolescents, and a community psychologist who contributed to the development of Opp through a workshop.

In addition to this, 27 adolescents participated in a user survey. The study indicated that Opp had good usability, and the overall mean star ranking of the app was 3.78 (SD 0.42) on a 5-point scale. A large proportion of the adolescents thought that Opp was interesting to use (20/27, 74%), that the design was good (25/27, 93%), and that it was appropriate for the target group (24/27, 89%) [20].

### Control

The waiting-list control group will receive the code to unlock the app after study completion.

### Randomization

This study is a cluster randomized controlled trial with intervention and waiting-list control groups. Schools will be randomly assigned to one of the groups by a statistician after baseline assessment. SPSS (IBM Corp) will be used to generate a random number between 0 and 1 that will be assigned to each school. The half of the schools with lower values for the random number will be assigned to the control group and the half of the schools with higher values will be assigned to the intervention group.

### Blinding

Neither schools, guardians, nor adolescent participants will know if they are assigned to the intervention or the control group prior to the baseline assessment.

### Outcomes

Data will be collected at 3 measurement points: baseline (T1; preintervention); approximately 2 weeks after the intervention (T2; postintervention); and approximately 1 month after the intervention (T3; follow-up) through self-report measures that the adolescents fill in using the secure online tool Nettskjema (University of Oslo).

### Primary Outcomes

Mental health will be assessed using the World Health Organization–5 Well-being Index (WHO-5) [21] and the Strengths and Difficulties Questionnaire (SDQ) [22]. Both the WHO-5 [23] and the SDQ [24] have been found to have adequate validity as outcome measures. The primary hypothesis is that there will be significant differences in changes in the mental health scores of the intervention and the control groups in favor of the intervention group.

### Secondary Outcomes

Coping skills will be measured with the Norwegian version of the General Self-Efficacy Scale [25]. A Norwegian study found that this scale had satisfactory internal consistency, test-retest reliability, and factor structure [26]. Help-seeking behavior will be assessed with 3 items that measure if the adolescents sought help, who they sought help from, and if they received the help they needed. The Self-liking and Competence Scale [27,28] will be used to measure self-liking and self-competence; this scale has been found to have good internal consistency and factor structure in a Norwegian validation study [29]. Sleep quality will be measured with six questions from the Bergen Child Study [30].

In addition to these measures, there will be app-specific questions in the second and third questionnaires for the intervention group that ask about how often and for how long the adolescents used the app and what features of the app they liked best.

### Power Calculations

Power calculations were conducted with PASS 16 (NCSS, LLC). Using multilevel analysis with a significance level of .05 will require a total sample of 1250 adolescents (625 in both the intervention and control groups, including 25 schools with 25 students per school) to achieve a power of .79 and to detect a small effect corresponding to Cohen *d*=0.20 when the expected interclass correlation at the school level is 0.02. Anticipating a drop-out rate of approximately 25%, a total of 1563 adolescents should be recruited [15].

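### The recruitment target of 1563 multiplies 1250 by 1.25 instead of dividing by 0.75, so it covers 20% dropout and not the stated 25%

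*Protocol article*

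**What the plan says.** All the figures stand in the protocol article, under Methods, Power Calculations. The analysis "will require a total sample of 1250 adolescents", described as "625 in both the intervention and control groups, including 25 schools with 25 students per school". The stated aim is "to achieve a power of .79" for Cohen d = 0.20, "when the expected interclass correlation at the school level is 0.02". The next sentence sets the recruitment target: "Anticipating a drop-out rate of approximately 25%, a total of 1563 adolescents should be recruited". A citation is attached to that sentence. The section gives no inflation formula and no definition of the dropout rate other than the percentage.

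**The concern.** A dropout rate is ordinarily the share of recruited participants who are lost. An allowance for it is therefore made by dividing the required number by the share retained. The stated target is exactly what results from adding 25% to the required number, which is a different operation and gives a smaller figure. If so, the required number, the dropout rate and the target, printed in two consecutive sentences, cannot all hold together. At stake is whether the target protects the sample size on which the power statement rests. The stated power is already just under .80, so the plan has little to spare.

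**Working it through.** **Inputs, all from Power Calculations.** Required N = 1250, 625 per arm. 25 schools × 25 students = 625, so 25 schools per arm and 50 in total. Significance level .05; sidedness is not stated, and two-sided is assumed here. d = 0.20, school-level intraclass correlation 0.02, stated power .79, dropout about 25%, target 1563.

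**Step 1. Reproduce the target.** N × (1 + dropout) = 1250 × 1.25 = 1562.5, which rounds up to 1563. The match is exact.

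**Step 2. The target that keeps 1250.** N/(1 − dropout) = 1250/0.75 = 1666.7, which rounds up to 1667. The stated target is 1667 − 1563 = 104 lower, or 104/1667 = 6.2%.

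**Step 3. What 1563 delivers.** 1563 × 0.75 = 1172.25, so about 1172 remain, and 1250 − 1172 = 78 are missing. The dropout rate at which 1563 does keep 1250 is 1 − 1250/1563 = 20.0%.

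**Step 4. Power at 1250 by the plain design-effect formula.**
- Design effect = 1 + (25 − 1) × 0.02 = 1.48.
- Standard error of d = √(1.48 × 2/625) = 0.0688.
- 0.20/0.0688 = 2.906, and 2.906 − 1.960 = 0.946, giving power .828 (normal).
- With a t reference on 50 − 2 = 48 df, power is .813.

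Neither equals the stated .79. Unequal school sizes could account for the gap: a coefficient of variation of about 0.4 with 48 df gives .792. The article does not state such an assumption.

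**Step 5. Power at 1172 by the same formula, 50 schools.**
- Students per school = 1172.25/50 = 23.4, and per arm 586.
- Design effect = 1 + (23.445 − 1) × 0.02 = 1.449.
- Standard error = √(1.449 × 2/586.1) = 0.0703.
- 0.20/0.0703 = 2.844, and 2.844 − 1.960 = 0.884, giving power .812 (normal), or .796 (t, 48 df).

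| N with complete follow-up | Normal | t, 48 df |
|---|---|---|
| 1250 | .828 | .813 |
| 1172 | .812 | .796 |
| Loss | .016 | .017 |

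**Step 6. Sensitivity.** If the loss came as fewer schools of 25 instead of fewer students per school, 1172 would give .804 (normal) or .786 (t), a loss of about 2.5 points.

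**The case against.** The strongest reply is that little follows from the slip. On the stated inputs with 50 schools, the plain formula gives .812 or .796 at 1172, which is not below the stated .79. That stands, and it limits what can be claimed.

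A second reply is that 1172 need not be the number analysed. Planned Statistical Analysis specifies linear mixed models over three measurement points and states no restriction to complete cases. Such models can use an adolescent who answers the second questionnaire but not the third. This also stands: the power loss above assumes that dropouts contribute nothing and may overstate the cost. It does not rescue the target, because the plan itself chose to inflate for dropout and did so with the wrong operation.

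A third reply is that the rate is only approximate. This fails. The target is exactly 1.25 times 1250, and the rate it accommodates is 20.0%. The citation attached to the sentence may support the choice of rate, but it cannot make 0.75 × 1563 equal 1250.

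A reader might go further and infer that true power is about .77, by rescaling the calculation so that 1250 gives .79. That requires changing d to about 0.194 or the intraclass correlation to about 0.024. Neither value is in the article and the PASS settings are not shown, so the figure is not the plan's. A reader might also take the parenthesis to mean 25 schools in total. Since 25 × 25 = 625 is given against each arm, 50 schools is the only reading consistent with 1250.

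**Conclusion.** The recruitment target is wrong on the article's own figures. It should be 1667 for 25% dropout; 1563 corresponds to 20%. The shortfall is 104 recruits, or 78 adolescents with complete follow-up. This part rests on nothing but the three printed numbers and the usual meaning of a dropout rate.

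The cost in power is about 2 points. That estimate assumes a two-sided test, 50 schools of equal size, dropout spread evenly over schools, and no contribution from dropouts. The inference that the stated power of .79 is not delivered goes beyond the document: the stated power cannot be reproduced exactly from the printed inputs, and the plain formula stays at about .80 or .81 after the planned dropout. No hypothesis or analysis changes. Severity is minor.

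**What to change.** Correct the one sentence, in either of two ways.

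- Give the target as 1667 for 25% dropout, which is 1667/50 = 33.3 recruits per school in 50 schools instead of 1563/50 = 31.3.
- Keep 1563, say that it covers 20% dropout and that 25% would leave about 1172 with complete follow-up, and report the power for 1172 recomputed in PASS with the settings that gave .79.

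The first costs 104 more recruits, about two per school. The Results section reports 381 first questionnaires so far and a prolonged collection period, so the second may be the more realistic. It costs one rerun of the power calculation and a slightly less favourable power statement.
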